# Elbow hemiarthroplasty versus open reduction and internal fixation for AO/OTA type 13 C2 and C3 fractures of distal humerus in patients aged 50 years or above: a randomized controlled trial

**DOI:** 10.1186/s13063-020-04418-8

**Published:** 2020-06-08

**Keywords:** Elbow, Hemiarthroplasty, Osteosynthesis, Humerus, Fracture, Randomized, Outcome, Reoperation, Complication

## Abstract

**Background:**

Intraarticular distal humeral fractures of AO/OTA type 13 C2 and C3 pose a surgical challenge despite the evolution of surgical implants and techniques. Open reduction and internal fixation (ORIF) is often preferred as the first choice of treatment, but the results vary and are sometimes disappointing. Total elbow arthroplasty (TEA) has been widely used for fractures that are not amenable to ORIF in elderly patients, but the mechanical complications remain a challenge, especially in active patients. Elbow hemiarthroplasty (EHA) provides a modern alternative that might avoid the mechanical complications and weight bearing restrictions related to the linked articulation in semi-constrained TEA. No studies have compared the results of EHA to that of ORIF, but case series have reported promising results.

**Methods/design:**

This is a study protocol describing an investigator-initiated, non-blinded randomized controlled trial comparing the outcome of EHA with ORIF for AO/OTA type 13 C2 and C3 fractures of the distal humerus in patients who are 50 years or older. Forty-four patients with AO/OTA type 13 C2 and C3 fractures of distal humerus will be randomized to either EHA or ORIF. The Oxford Elbow Score (OES) will be used as primary outcome. Mayo Elbow Performance Score (MEPS), pain severity score (VAS), range of motion, and patient satisfaction will be used as secondary outcomes. Reoperations, complications, and the length of sick leave will be recorded. The patients will be examined after the operation and at 3 months and 1, 2, 5, and 10 years.

**Discussion:**

The main objective of this study is to investigate the best treatment option for AO/OTA type 13 C2 and C3 fractures of distal humerus in patients aged 50 years or above. We hypothesize that EHA results in fewer complications and superior functional outcome compared with ORIF and that the mechanical complications related to the linked articulation of TEA can be avoided.

**Trial registration:**

ClinicalTrials.gov, PRS, NCT04163172. Registered November 13, 2019. https://clinicaltrials.gov/ct2/results?cond=&term=evori&cntry=&state=&city=&dist= (Table 2).

The protocol has been approved by The Scientific Ethics Committee of the Capital Region of Denmark (Jr. no.: H^− 19,035,590^).

The processing of personal data has been approved by the Danish Data Protection Agency (Jr. no. P-2019-246). Inclusion started on February 1, 2020.

## Background

Adult distal humeral fractures comprise 2% to 5% of all fractures and 30% of all elbow fractures [2, 22]. Despite the evolution of surgical implants and techniques, AO/OTA type 13 C2 and C3 fractures of the distal humerus still pose a surgical challenge. Open reduction and internal fixation (ORIF) is often preferred as the first choice of treatment, but the results vary and are sometimes disappointing, especially in elderly patients [10, 25, 29]. The success of ORIF depends on correct reduction of the fracture, reconstruction of the articular surface, and the stability and rigidity of the fixation [12]. Total elbow arthroplasty (TEA) has been widely used during the last 20 years for fractures in elderly patients that are not amenable to ORIF, but the mechanical complications related to the linked articulation remain a challenge [7, 23, 27]. Unlinked TEA has been used to minimize the mechanical complications of the linked TEA, but the joint instability is a major complication, especially in condylar displacement, and the survival rate and functional results may be lower than for the linked arthroplasty [14, 16, 30, 31]. Elbow hemiarthroplasty (EHA) provides a modern alternative that might avoid the mechanical complications and weight bearing restriction related to the linked articulation in TEA [1, 19, 20, 24, 26].

Currently, EHA has not been compared to ORIF, but previous studies comparing the outcomes of TEA and ORIF in elderly patients with an intraarticular distal humeral fracture concluded that good outcomes may be obtained with both procedures, but TEA resulted in more predictable outcome with fewer reoperations and major complications [8, 9, 11, 17].

The objective of this study protocol is to describe the methodology for an investigator-initiated, randomized controlled trial comparing the outcomes of EHA and ORIF for AO/OTA type 13 C2 and C3 fractures of distal humerus in patients who are 50 years or older. The Standard Protocol Items Recommendations for Interventional Trials (SPIRIT) Statement 2013 has been followed for the completion of this protocol (Table 1 and Additional file 1).

**Table 1 Tab1:**
[figure not shown]
Standard Protocol Items Recommendations for Interventional Trials diagram (SPIRIT)

* EHA group operated with Latitude anatomical hemiarthroplasty (WRIGHT, Memphis, TN, USA)

** ORIF group operated with double plates (Synthes, Switzerland and West Chester, PA, US)

****OES* Oxford Elbow Score

*****MEPS* Mayo Elbow Performance Score

## Methods/design

### Study design and aim

This is an investigator-initiated randomized controlled trial. The main objective of the study is to compare cemented hemiarthroplasty with open reduction and internal fixation of AO/OTA type 13 C2 and C3 fractures of the distal humerus in patients aged 50 years or above.

### Subjects

Forty-four patients with AO/OTA type 13 C2 and C3 fractures of the distal humerus randomized to either EHA or ORIF.

### Inclusion criteria

AO/OTA type 13 C2 and C3 fractures of the distal humerus confirmed by plain radiographs with two perpendicular views and CT scanASA score 1–3 and physically fit for surgeryAge of 50 years or above

### Exclusion criteria

Patients unable to follow the rehabilitation protocol or answer the Danish questionnaires because of physical or cognitive inabilities as evaluated by the recruiting surgeonSignificant elbow osteoarthritis as evaluated by the recruiting surgeon based on plain radiographs and CT scanFractures that are older than 6 weeksOther associated elbow fracturesPathological fractures or relevant elbow pathology

### Screening and data collection preoperatively

Gender and agePlain radiographs with standard anterior-posterior and lateral projectionsCT scan of the injured elbow joint

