### Randomization and concealment of allocation

Based on the sample calculation, we intend to include a total number of 44 patients allocated into two groups of equal size:
EHA (elbow hemiarthroplasty)—intervention groupORIF (open reduction and internal fixation)—comparator group

The randomization is done just prior to the operation by the primary investigator, who will inform the operation team about the intended surgery. The randomization sequence will be computer generated using RED-Cap (Research Electronic Data Capture) program. The patients will be randomized using stratified, block randomization with a 1:1 allocation ratio and stratified according to age in years (50–69, 70 and above) and sex. The randomization sequence is generated by a statistician, and the patients will be stratified and then randomized. After randomization, the patient’s allocation will be revealed to the operation team to unpack the necessary operation tools and prosthesis.

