### Outcome measures

#### Primary functional outcome

The Oxford Elbow Score (OES) will be used to assess the primary outcome at 2 years.

The OES is a 12-item, patient-administrated questionnaire that measures the quality of life in patients with an elbow disorder. There are three unidimensional domains: elbow function, pain, and social-psychological status [5, 13]. Each question is answered on a five-point scale with each question contributing equally to the total score. Thus, the total score ranges from 12 to 60, with 60 being the worst. For ease of presentation the score is converted to a scale from 0 to 48 with 48 being the best. The outcome can be interpreted based on a 48-point scale: 0–19, poor; 20–29, fair; 30–39, good; and 40–48, excellent [6]. The Danish version, which will be used in this study, has been translated and culturally adapted according to the guidelines by Guillemin, Bombardier, and Beaton [6, 21].

The minimal clinically important differences (MCID) for the total score of OES has not been defined, but Dawson et al. reported the MCID for each of the three domains, pain, function, and social-psychological. The MCID for the three domains was 19, 9, and 18, respectively [5]. Accordingly, we estimated the MCID for the total score to be 15.

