### Follow-up

All patients will be followed actively for 10 years. To ensure the implant position, all patients will undergo a plain x-ray in two planes before discharge, which will usually be done on the first postoperative day. Then all patients will be followed actively with plain radiographs, clinical outcome, and patient-reported outcome at 3 months postoperatively and at 1, 2, 5, and 10 years.

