### Protocol violations, patient drop-out, and revision

The number of patients who receive the allocated treatment will be reported. If ORIF is technically impossible, the surgeon remains free to use an EHA if it is believed to be in the best interest of the patient. A main analysis will be conducted on an intention-to-treat basis where all outcome scores from each patient are analyzed according to the randomization, irrespective of type of surgery received. If operative crossover does occur, a secondary analysis will be conducted on a per protocol basis. This analysis will only include patients who undergo surgery according to the randomization.

Patients who drop out of the trial will be recorded, and the reason for the drop-out will be noted. The patient will be included in the analysis with the latest follow up (last observation carried forward). Drop-outs before the 3-month evaluation cannot be included in the analysis due to lack of preoperative data. The number of patients who do not comply with rehabilitation will be recorded.

If a reoperation is needed, the reason and the operation type are recorded. If possible, the patient is evaluated using clinical outcome and patient-reported outcome prior to the revision procedure. The patient will remain in the study and they are included in the analysis with their latest follow-up.

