#### Data analysis

No interim data analysis will be carried out before the analysis at 2 years. Baseline characteristics and outcome scores will, for each group, be summarized by number and percentage (categorical data) and mean and standard deviation or median and interquartile range, as appropriate (continues data). No statistical tests of differences in baseline characteristics between the two groups will be conducted as any difference must be due to chance and not bias. The differences in outcome scores between the two groups will be analyzed with use of parametric statistics (Students *t*-test) or non-parametric statistics (Mann-Withney U-test) as appropriate. Categorical data will be analyzed with use of chi-square test.

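### The C2/C3 fracture grade, needed for entry and read on the preoperative CT, is not a listed baseline item, a stratum or a covariate; the cost is modest and the remedy nearly free

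*Protocol article*

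**What the plan says.** Under Screening and data collection preoperatively, the protocol article lists "Gender and agePlain radiographs with standard anterior-posterior and lateral projectionsCT scan of the injured elbow joint" (the run-together words come from the text extraction). No fracture grade and no elbow score is named.

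Under Inclusion criteria, the fracture must be AO/OTA type 13 C2 or C3, confirmed on two-view radiographs and CT. The images needed for the grade therefore exist before the draw.

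The Background says: "The success of ORIF depends on correct reduction of the fracture, reconstruction of the articular surface, and the stability and rigidity of the fixation".

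Randomization and concealment of allocation describes "stratified, block randomization with a 1:1 allocation ratio", "stratified according to age in years (50–69, 70 and above) and sex". Grade is not a stratum.

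On the outcome: "The Oxford Elbow Score (OES) will be used to assess the primary outcome at 2 years". Data analysis says: "The differences in outcome scores between the two groups will be analyzed with use of parametric statistics (Students *t*-test"), with the Mann-Whitney test as the alternative and chi-square for categorical data. No covariate is named. The same section promises a summary of baseline characteristics by arm without listing them.

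**The concern.** On the protocol's own account, how well the joint surface can be reconstructed decides how well one of the two treatments works. C2 versus C3 is the one marker of fracture complexity that must be settled for every patient before entry. A plan that neither lists it as data nor uses it leaves known information aside in a trial of 44.

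Two things are at stake. First, if grade predicts 2-year OES, an unadjusted comparison carries that variation in its error term. Second, apart from images, the listed baseline items are age and sex, which stratification already balances. A baseline table built from that list would not show whether one arm happened to receive more C3 fractures. The same gap affects the per-protocol analysis, which drops ORIF patients converted to EHA. If those were the more complex fractures (the protocol does not say so), a grade recorded beforehand would help a reader see the selection.

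**Working it through.** **Inputs from the protocol article (Sample size calculation OES).** SD 16; difference 15; 18 evaluable per group; 44 in all with 18% drop-out.

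**Assumptions, not in the documents.** Half the fractures are C3 (30% to 70% for the imbalance probabilities). C3 scores 5 to 10 OES points below C2 at 2 years.

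**The plan's own figure.** n per group = 2 × (z₁₋α/₂ + z₀.₈₀)² × (16/15)².
- Two-sided alpha 0.05: 17.9, so 18; and 36/(1 − 0.18) = 43.9, so 44. This matches.
- The printed alpha of 0.005: 30.3, so 31. This does not match.

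That discrepancy is a separate matter. Only SD 16 and 18 per arm are used below.

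**Step 1: chance imbalance in grade.**
- SD of the between-arm difference in C3 share = √(2 × 0.5 × 0.5/18) = 0.167.
- 95% range: 1.96 × 0.167 = 0.327, about ±33 percentage points.
- Exact binomial chance that the arms differ by at least 20 percentage points: 20% to 24% at 18 per arm, and 14% to 17% at 22 per arm (C3 share 30% to 70%).

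**Step 2: what that does to the arm difference.**
- SD of the shift: 0.167 × 5 = 0.8 points; 0.167 × 10 = 1.7 points.
- 95% extreme: 0.327 × 5 = 1.6 points; 0.327 × 10 = 3.3 points, against a target of 15.

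**Step 3: share of variance explained by grade.** This is 0.25 × gap²/16².
- Gap 5: 6.25/256 = 2.4%.
- Gap 10: 25/256 = 9.8%.

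**Step 4: precision.**
- Unadjusted SE = 16 × √(2/18) = 5.33; half-width = 1.96 × 5.33 = 10.45.
- With the explained variance removed: 10.45 × √(1 − 0.024) = 10.3 and 10.45 × √(1 − 0.098) = 9.9. The gain is 0.1 to 0.5 points.

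**Step 5: what adjustment costs.**
- With equal arms and half C3, the correlation between arm and grade equals the difference in C3 share. The adjusted variance is therefore inflated on average by about 1/(1 − 0.167²) = 1.03.
- Net variance ratio: (1 − 0.024) × 1.03 = 1.00 at a gap of 5, and (1 − 0.098) × 1.03 = 0.93 at a gap of 10. A simulation of the adjusted and unadjusted estimates gave 1.01 and 0.93.
- Adjusting for grade, age group and sex uses three more degrees of freedom: 36 − 2 = 34 becomes 36 − 5 = 31. The t multiplier rises from 2.032 to 2.040.

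The figures in Step 4 are therefore the best case. At the small end of the assumed gap, adjustment for grade roughly breaks even on precision; at the large end it removes about 7% of the variance.

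**The case against.** The strongest reply is that nothing is contradicted or misstated. Chance imbalance in grade is already part of the outcome variance, so the t-test's standard error allows for it and the test is valid. Baseline lists and covariates are often settled in a full protocol or SAP. Table 1 is not shown, and the promised baseline summary may include more than the preoperative list. The preoperative CT also preserves the evidence, so the grade can be read later by someone unaware of the allocation. All of this stands, and it is why the point concerns efficiency and transparency rather than validity. It does not remove the point, because the comparison the article states has no covariate.

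A reader might go further in four ways that the documents do not support.

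- **That an observed difference would be biased by case mix.** Randomisation rules out systematic bias; only chance imbalance remains.
- **That the unblinded team will grade fractures after surgery, knowing the implant.** No section plans post-operative grading.
- **That nothing but age and sex is known before the draw.** ASA class and significant osteoarthritis are judged at entry, images are taken, and consent opens the medical record.
- **That a pre-injury OES is a required baseline.** The article does confirm that no preoperative score exists: "Drop-outs before the 3-month evaluation cannot be included in the analysis due to lack of preoperative data". All scores are taken "at 3 months postoperatively and at 1, 2, 5, and 10 years". But significant osteoarthritis and relevant elbow pathology are excluded, so recalled scores would probably sit near the ceiling of 48. They would be recalled after an acute fracture and would be missing for patients already operated on. A correlation of 0.3 to 0.5 with the 2-year score would remove 9% to 25% of the variance (0.3² to 0.5²), but nothing in the documents supports that correlation.

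**Conclusion.** The point holds in a limited form. A characteristic that must be established for entry, and that bears on what the protocol treats as decisive for ORIF, is absent from the listed preoperative data, the strata and the stated comparison. The trial remains valid without it.

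The gain is modest. Grade explains about 2% to 10% of the variance, and the half-width falls by at most 0.1 to 0.5 points from 10.5. After the cost of adjustment, the net change in variance runs from nil to about 7%. These figures rest on an assumed 50% C3 share and an assumed gap of 5 to 10 points.

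The benefit that does not depend on the assumed gap is visibility. With 18 per arm, a difference of 20 percentage points or more in C3 share has roughly a one-in-five to one-in-four chance, and the listed items would not display it. Because the remedy costs so little, the change is worth making. An unshown item in Table 1 or in a fuller document could already meet the recording part.

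**What to change.** 1. **Screening and data collection preoperatively:** add the CT-based C2 or C3 grade as a REDCap field, completed before randomisation. For patients already enrolled (inclusion began February 1, 2020), take the grade from the entry CT, read without knowledge of allocation.
2. **Data analysis:** report the grade by arm. State that the 2-year OES difference is estimated by a linear model adjusted for C2/C3, age group and sex, with the unadjusted test as a sensitivity analysis. Including age group and sex brings the analysis into line with the stratified draw, and naming one model settles how adjustment sits beside the t-test or Mann-Whitney choice.
3. **Stratification:** leave as it is. Adding grade would turn 2 × 2 = 4 strata into 8, or 44/8 = 5.5 patients each.
4. **Pre-injury OES:** optional as a descriptive item; not a required covariate.

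The cost is one data field, a blinded reading of existing CTs for those already enrolled, three degrees of freedom and some grading error. Sample size and treatment are untouched.

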### Eligibility

All Danish citizens aged 50 years or above with AO/OTA type 13 C2 and C3 fractures of the distal humerus referred to the orthopedic department at Herlev and Gentofte University Hospital will be offered participation in the trial. The patients will receive oral and written information about the study by the operating surgeon or by the primary investigator. They will have at least 24 h to consider participation in the study before informed consent is obtained. They will also be informed that they can withdraw their consent at any time. The informed consent gives the primary investigator access to information about the patient’s health condition from the medical record. The study will follow the Helsinki Declaration.

All the operations will be performed at the orthopedic department at Herlev and Gentofte University Hospital, which is the largest referral shoulder and elbow unit in Denmark. Fifteen to twenty patients with this type of fracture have been treated at the department each year from 2016 to 2018. With this number of patients, we estimate that a 3-year recruitment period from February 1, 2020 to December 31, 2022 will allow inclusion of the planned number of patients.

### Randomization and concealment of allocation

Based on the sample calculation, we intend to include a total number of 44 patients allocated into two groups of equal size:
EHA (elbow hemiarthroplasty)—intervention groupORIF (open reduction and internal fixation)—comparator group

The randomization is done just prior to the operation by the primary investigator, who will inform the operation team about the intended surgery. The randomization sequence will be computer generated using RED-Cap (Research Electronic Data Capture) program. The patients will be randomized using stratified, block randomization with a 1:1 allocation ratio and stratified according to age in years (50–69, 70 and above) and sex. The randomization sequence is generated by a statistician, and the patients will be stratified and then randomized. After randomization, the patient’s allocation will be revealed to the operation team to unpack the necessary operation tools and prosthesis.

### Interventions

All patients will be operated on by one of three experienced elbow surgeons in order to secure a high surgical standard. The treatment is standardized; all patients have a tourniquet and are placed in a lateral supine position. A posterior midline approach will be used, and the ulnar nerve will be identified and protected in situ without transposition. All procedures are performed using a triceps-split.

#### The Latitude anatomical hemiarthroplasty (WRIGHT, Memphis, TN, US)

The prosthesis will be used according to the manufacturer’s manual. A trial component will be inserted, and range of motion and stability will be evaluated before the component is inserted using a standard cementing technique. The medial and lateral epicondyles, with the collateral ligaments attached, will be fixated to the arthroplasty using this FiberWire suture (Arthrex, Naples, FL, USA) and subsequently to the humerus using additional FiberWire sutures. In patients with a preserved medial column, the medial ligament will not be detached during the procedure.

#### Double plating (Synthes, Switzerland and West Chester, PA, US)

The fracture will be reduced and the articular surface will be reconstructed as well as possible. The fracture will then be fixated with two plates—parallel or perpendicular according to the fracture nature. The collateral ligaments will be attached to the plates using FiberWire suture (Arthrex, Naples, FL, USA). The stability and rigidity of the fixation will be checked.

Standard closure with absorbable sutures and reinsertion of the collateral ligaments with non-absorbable sutures will be performed. Standard skin closure is with with metal clamps. All patients will receive standard pre-, peri-, and post-operative pain management, including general anesthesia and interscalene peripheral nerve block performed by the anesthesiologist. The pain management can be adjusted and individualized if needed. There is no collection and storage of biological specimens for genetic or molecular analysis.

